## Abstract

**Background:**

Interpretive front-of-pack nutrition labels are better understood than non-interpretive labels. However, robust evidence on the effects of such labels on consumer food purchases in the real-world is lacking. Our aim is to assess the effects of two interpretive front-of-pack nutrition labels, compared with a non-interpretive label, on the healthiness of consumer food purchases.

**Methods/Design:**

A five-week (1-week baseline and 4-week intervention) three-arm parallel randomised controlled trial will be conducted using a bespoke smartphone application, which will administer study questionnaires and deliver intervention (Multiple Traffic Light and Health Star Rating) and control (Nutrition Information Panel) labels. To view their allocated nutrition label, participants scan the barcode of packaged food products using their smartphone camera. The assigned label is displayed instantly on the smartphone screen.1500 eligible participants (New Zealand adult smartphone owners who shop in a supermarket at least once a week and are main household shoppers) will be randomised in a 1:1:1 ratio to one of the three nutrition label formats, using computer-generated randomisation sequences. Randomisation will be stratified by ethnicity and interest in healthy eating. Food and beverage purchase data will be collected continuously throughout the study via hard copy till receipts and electronic grocery purchase lists recorded and transmitted using the smartphone application. The primary outcome will be healthiness of food purchases in each trial arm, assessed as mean Food Standards Australia New Zealand nutrient profiling score criterion score for all food and beverages purchased over the intervention period. Secondary outcomes will include saturated fat, sugar, sodium and energy content of food purchases; food expenditure; labelling profile of food purchases (i.e. mean number of Health Star Rating stars and proportion of red, green and amber traffic lights); nutrient profiling score over time and by food categories; purchases of unpackaged foods; self-reported nutrition knowledge and recorded use of assigned labelling system.

**Discussion:**

The Starlight randomised, controlled trial will determine the effects of interpretive front-of-pack nutrition labels on the healthiness of consumer food purchases in the real world.

**Trial registration:**

Australian New Zealand Clinical Trials Registry ACTRN12614000644662 (registered 18 June 2014).

## Background

Obesity and the burden of associated non-communicable disease has been increasing worldwide [1]. Effective, front-of-pack (FOP) nutrition labelling is potentially one of the most cost-effective interventions [2]. However, traditional numerical nutrition labels are difficult to interpret and have limited influence on the average consumer’s food purchasing patterns [3–5].

In New Zealand, the Nutrition Information Panel (NIP), usually found on the back of food packages, is mandatory [6]. A review of nutrition label use found that this is poorly understood by most New Zealanders [7]. Further, use of this nutrition label is particularly low among Māori (indigenous New Zealanders), Pacific, and low-income New Zealanders [8], who experience the highest rates of obesity [9]. Therefore, identifying a labelling format that delivers information effectively to these groups is especially important.

A recent review of New Zealand and Australian food labelling policy recommended introduction of interpretative FOP labels that are easy for consumers to understand and act upon [10]. Substantial global evidence indicates that interpretative labels (using graphics, symbols or colours) are better understood than traditional numeric nutrition labels [11]. However, the impact of such labels on food purchase habits is unclear.

Evaluation of nutrition labelling interventions in the real-world is challenging. Two common approaches are to use controlled settings (for example, a workplace cafeteria or one particular retailer), or consumer surveys. Several cafeteria studies support the ability of FOP labels to promote healthy food choices [12–14]. Surveys and choice experiments also report favourable results, suggesting FOP labels help participants to successfully identify healthier options [15] and are used to make food choices [16–18].

A limited number of studies report on the effect of FOP labels in retail settings. A large observational study conducted by Sacks et al. [19] investigated the effect of supplementary traffic-light FOP labels implemented as a voluntary nutrition labelling system in a UK retailer. The study reported no difference between sales of healthy and unhealthy ready meals and sandwiches following introduction of traffic-light FOP labels, compared to the period prior to label administration. The major limitation of this study was the small sample of products included in the study. Another large intervention study assessed the effectiveness of “Guiding Star” shelf labelling system across a chain of 168 US supermarkets [20]. Analysis of supermarket sales data showed a significant increase in proportion of star-rated product sales and corresponding decrease in sales of un-starred products in same food categories [20]. One limitation however was the lack of a control group within the same stores. Randomised controlled trials are needed to provide robust evidence on the effect of the FOP labels on real-world retail food purchases.

The current study assesses two types of FOP nutrition labels. One is the colour-coded traffic-light (TL) FOP label [21]. This label uses colour-coded categories to reflect low (green), medium (amber) and high (red) content of four nutrients: total fat, saturated fat, total sugar and salt. The underpinning algorithm is that recommended by the UK Governments [22]. This FOP label has been shown to have a high level of understanding and acceptance across major ethnic and income groups [23]. The other label to be evaluated is the new Health Star Rating (HSR) system proposed for implementation in Australia. This label assigns a star rating to a food from ½ (least healthy) to 5 (most healthy) stars based on the underpinning HSR score algorithm [24].

The intervention will be delivered using novel smartphone technology, based on the FoodSwitch free smartphone application (app) where users scan the barcode of a packaged food and receive an immediate, interpretive TL nutrition label on their phone screen, and recommendations for healthier options [25]. A similar smartphone app designed for the current study will be used to deliver TL, HSR or NIP nutrition labels to study participants. The primary aim of the trial is to assess the effectiveness of TL and HSR label formats, compared with the standard NIP, on healthiness of consumer food purchases. The null hypothesis of no difference with the control label will be tested for each of the intervention arms.

## Methods/Design

### Study design

Starlight is a three-arm parallel randomised controlled trial (Figure 1). A total of 1,500 participants will be randomised to receive either one of two FOP labels (TL or HSR; intervention arms) or NIP label (control arm) in a 1:1:1 ratio. All nutrition labels will be delivered via a bespoke “Food Label Trial” smartphone app.

**Figure 1 Fig1:**
[figure not shown]
**Flow chart for the Starlight trial.**

### Approval

Ethical approval from the University of Auckland Human Participants Ethics Committee was received on 26 May 2014. The Starlight trial is registered in the Australian New Zealand Clinical Trials Registry (registration number ACTRN12614000644662).

**Intervention arms**FOP Traffic-Light label (Figure 2a).FOP Health Star Rating label (Figure 2b).

**Figure 2 Fig2:**
[figure not shown]
**Example of intervention label formats. a)** Traffic-lights FOP label **b)** Health Star Rating FOP label **c)** New Zealand NIP label.

**Control arm:**Standard New Zealand non-interpretive, numerical NIP (Figure 2c)

### “Food Label Trial” smartphone application

All allocated labels will be delivered via the bespoke “Food Label Trial” smartphone app, which enables participants to view the allocated nutrition label for packaged barcoded products. To view the label, users scan barcodes of packaged food products using the smartphone camera, and assigned labels instantly appear on the phone screen. At the same time the app also displays a random selection of other foods in the same food category with same label format to encourage comparative review of available choices and to better test the influence of the label on purchasing decision. If a food item is missing from the app database, participants will receive a default message and will have an option of providing the details of this product (photographs and barcode) in order for it to be added to the database.

Additional app functions enable outcome data collection. Participants will use the app to create electronic lists of purchased food/beverage products and to photograph their grocery till receipts. In order to create the electronic list of purchased items the participants will scan barcodes of the items purchased using their smartphone camera.

### Study population

The Starlight trial will recruit 1500 New Zealand adults (aged 18 years and older) who have a smartphone (iPhone or Android), are main household shoppers (i.e. complete 50% or more of the grocery shopping for their household), and shop at a supermarket at least once a week. Participants must be able to read and understand English, and be available for the full duration of the 5-week trial. Only one person per household can participate in the study. Current or previous FoodSwitch app users will be excluded, because FoodSwitch provides TL labels and recommends healthier food options.

### Recruitment and run-in phase/baseline

Participants will be recruited across New Zealand via advertising in local newspapers and on social media websites, household mail drops, at community venues including supermarkets, and utilising existing research team networks. The aim is to recruit approximately equal numbers of Māori (n = 500), Pacific (n = 500) and other ethnic group participants (n = 500).

Eligible participants will be given access to the “Food Label Trial” app. Informed consent and baseline demographic data will be collected from all study participants via the app.

During the run-in/baseline phase participants will record their food and beverage purchases for one week using the app, and collect and photograph the corresponding till receipts using the smartphone app. At least 15 purchased barcoded grocery items will need to be recorded during this period in order to qualify for study entry. Failure to complete the run-in phase will result in ineligibility.

### Randomisation

Participants who complete the run-in phase successfully will be randomised in a 1:1:1 ratio to one of the three label formats (TL; HSR or NIP), using a central computer-based randomisation system. Blocked randomisation will be used with variable block sizes, stratified by self-identified ethnic group (Māori, Pacific, Other) and self-reported interest in “healthy eating” (not particularly interested; moderately to very interested).

### Blinding

It is not possible to blind trial participants to the intervention. However, participants will only see one type of label for the duration of the trial and will not know what other label formats are being tested in the trial.

### Data collection

The baseline questionnaire will collect demographic details (age, gender, ethnicity, income, education level, family size) and self-reported information on interest in nutrition and healthy eating.

Data on participant food and beverage purchases will be collected throughout the one-week baseline and four-week intervention period. Usage of the labelling function will be automatically recorded by the “Food Label Trial” app. Objective purchase data will be supplied by participants in the following modes: 1) electronic list of scanned purchased items (“Food Label Trial” app function); 2) photographs of corresponding grocery till receipts (“Food Label Trial” app function); 3) hard copies of grocery till receipts (returned by participants at the end of the intervention period). The electronic lists of purchased items will be used as the primary data source of packaged food purchases. The till receipts provide information on price and on purchases of non-barcoded items. Photographs of till receipts will be used as a back-up for missing hard copy till receipts.

All data collected via the “Food Label Trial” will be automatically transmitted via Wi-Fi or 3/4G to the app database, hosted on a remote server, and subsequently extracted by researchers to the study database. Hard copies of till receipts will be mailed by participants to the study centre and the additional data manually entered into the study database.

A follow up questionnaire will collect participant feedback on the app (technical issues, usefulness, self-reported impact on food choices), self-reported compliance with the trial protocol (number of shopping events recorded and till receipts returned, usage of the trial app) and perceived changes in participant’s nutrition knowledge.

Regular reminder messages (3 times per week) will be sent throughout the intervention period to encourage participants to use the app and submit data, and to minimise attrition. At the end of the study participants will be provided with reward vouchers as a compensation for the time and potential costs associated with taking part in the trial.

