### Statistical analyses

Statistical analyses will be performed using SAS version 9.3 (SAS Institute Inc. Cary NC). All statistical tests will be two-tailed and maintained at a 5% significance level. The baseline characteristics of all study participants will be summarised and tabulated using means (standard deviations, medians and ranges) and frequencies (proportions). Analysis of covariance (ANCOVA) regression models will be used to compare mean nutrient profiling score between intervention and control groups, adjusting for baseline nutrient profiling score and stratification factors. A similar approach will be used for continuous secondary outcomes. Generalized linear models will be used for secondary categorical outcomes. No imputation will be undertaken. Repeated measures mixed models will be used to evaluate treatment effects over time. Sub-group analyses will test possible interactions of the labelling intervention with key food categories, ethnicity (Maori, Pacific, Other), income tertile, and baseline self-reported interest in “healthy eating”. Sensitivity analyses will be undertaken using data only from participants who return at least 75% of till receipts/food purchase data based on pre-randomisation usual reported number of shopping episodes. A statistical analysis plan will be prepared by the trial statistician prior to the final data lock. Reporting will adhere to the CONSORT 2010 guidelines for reporting parallel group randomised trials.

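### Packaged-food purchases in the primary outcome are the items that unblinded participants choose to scan, and the stated uses of the till receipts include no check for unscanned items

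*Protocol article*

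**What the plan says.** The primary outcome (Outcomes section) is the mean nutrient profiling score of everything bought over the four intervention weeks. Four statements decide which packaged items enter it.

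- How the list is made (smartphone application section): "In order to create the electronic list of purchased items the participants will scan barcodes of the items purchased using their smartphone camera".
- Which source counts (Data collection): "The electronic lists of purchased items will be used as the primary data source of packaged food purchases".
- What receipts are for (Data collection): "The till receipts provide information on price and on purchases of non-barcoded items". For the paper copies: "Hard copies of till receipts will be mailed by participants to the study centre and the additional data manually entered into the study database". For the photographs: "Photographs of till receipts will be used as a back-up for missing hard copy till receipts".
- Blinding: "It is not possible to blind trial participants to the intervention", although participants "will not know what other label formats are being tested in the trial".

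The one analysis that deals with completeness is in Statistical analyses: "Sensitivity analyses will be undertaken using data only from participants who return at least 75% of till receipts/food purchase data". Its benchmark is the usual number of shopping episodes reported before randomisation. The same section states that nothing will be imputed.

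**The concern.** A packaged item counts only if the participant scans it into the list, so the participant controls inclusion. The interpretive formats mark an unhealthy product visibly, with a red light or a low star rating. The control panel gives numbers that the Background describes as poorly understood. The cue to leave an item off the list could therefore differ by arm.

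A lower score is healthier (Sample size section). If unhealthy items are dropped more often in an interpretive arm, that arm's mean falls with no change in what was bought, in the same direction as a true benefit. The receipts are a second record of the same baskets, yet no stated step uses them to look for packaged items that were bought but not scanned. The article describes the purchase data as objective, which is accurate for the scanned items but not for the decision to scan them.

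**Working it through.** **1. The plan's own figure.** Inputs from the Sample size section: 500 per arm, 2-unit difference, SD 9.9, adjustment for multiple comparisons. I take this as two-sided alpha 0.05/2 = 0.025 for two comparisons with control.

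- SE of an arm difference = 9.9 × √(2/500) = 0.626.
- Power = Φ(2/0.626 − 2.241) = Φ(0.953) = 83.0%. This agrees with the stated minimum of 80%.
- Smallest significant difference = 2.241 × 0.626 = 1.40 units.

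**2. Shift from omission in one arm.** Assumptions: item scores are normal with SD 9.9, there is no true label effect, only packaged items are considered, and a fraction d of items at least 9 points above the mean goes unscanned in one arm beyond whatever is omitted in the control arm. The document gives no omission rates, so d is an assumption.

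- Threshold: 9/9.9 = 0.909, so P(Z > 0.909) = 0.182 of items are in this group.
- Their mean excess over the overall mean = 9.9 × φ(0.909)/0.182 = 9.9 × 0.264/0.182 = 14.4 units.
- With q = 0.182 × d, shift = −q × 14.4/(1 − q).

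| d | q (share of all items) | Shift in arm mean | Chance of a significant result at 0.025 |
|---|---|---|---|
| 5% | 0.9% | −0.13 | 2.8% |
| 10% | 1.8% | −0.27 | 3.8% |
| 25% | 4.5% | −0.68 | 12.6% |

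The last column is 1 − Φ(2.241 − |shift|/0.626) + Φ(−2.241 − |shift|/0.626). It would be 2.5% with no omission.

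**3. A broader group of items.** If the least healthy third (33%) is affected, shift = −9.9 × φ(z) × d/(1 − 0.33d), where z cuts off the top 33% and 9.9 × φ(z) = 3.585. For d of 10%, 20%, 30% and 40% the shift is −0.37, −0.77, −1.19 and −1.65, and the chance of a significant result is 5%, 16%, 37% and 65%. A spurious 2-unit effect needs d of about 47%, or about 15.5% of all items, missing in one arm only.

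**4. Would a stated safeguard show it?**

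- *Baseline adjustment.* Randomisation follows the run-in, so baseline lists are made before the allocated label is seen. Omission prompted by that label starts afterwards and is not adjusted away.
- *Minimum of 15 recorded items.* This applies to the run-in only.
- *75% sensitivity set.* It is benchmarked on shopping episodes. A participant who records every shop but leaves some items out of each one passes in full.
- *Same app in every arm.* The Discussion says this neutralises any effect of scanning. That holds only if completeness of scanning does not depend on label format, and no stated analysis examines this.

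**The case against.** The strongest reply is that the article is silent on a check and does not exclude one. It does not say that receipts serve only for price and non-barcoded foods, and calling the list the primary source leaves room for another. A full protocol or the announced statistical analysis plan may contain reconciliation. This stands as a limit on the claim. The point survives because the article does fix where packaged purchases come from, what receipts are used for and which receipt data are entered, and scan-to-receipt comparison is not among them.

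The mechanism is also unproven. The article does not say that scanning an item into the purchase list displays its label, or that participants view a label for everything they buy; label use is itself an outcome. Control participants may leave out unhealthy items too, and only a difference between arms biases the comparison. The common app, ignorance of the other formats and the reminders three times a week all lower the risk. These points stand, which is why the bias is conditional.

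Two stronger readings are tempting. A reader might infer that modest omission would by itself give a significant result. On the plan's SD it would not usually do so: even −0.68 is about half of 1.40. The SD of 9.9 describes foods, and if participant means vary less the threshold falls in proportion (it is 0.142 × SD), but the document gives no participant-level SD and so supports no smaller threshold. A reader might also infer that such a bias could never be separated from a real effect. The retained receipts allow exactly that check.

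**Conclusion.** The concern holds as a conditional one. For packaged foods the primary outcome depends on what unblinded participants choose to scan, and the stated plan has no step that would show whether the completeness of scanning differs by arm. If it differs for unhealthy items, the comparison is biased, and towards the interpretive labels if they prompt the greater omission.

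The size is unknown. The illustrative shifts of 0.13 to 0.68 units rest on assumed omission rates, normal item scores, an SD taken from a food database rather than from baskets, and packaged items alone. If receipt-derived non-barcoded foods enter the mean, the shift is diluted. Against a threshold of about 1.40 units, such shifts would more probably inflate or add to an observed difference than create a significant one alone; the much heavier omission in step 3 would be needed for that. The point is worth acting on because the check is cheap, not because bias has been shown.

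**What to change.** 1. When receipts are entered for price, flag each packaged food line that has no counterpart in the participant's scanned list. Do this blind to arm, on all receipts or on a random sample.
2. Report the item capture rate (scanned items divided by packaged food lines on the receipt) by arm and by period, baseline and intervention.
3. Before data lock, pre-specify a sensitivity analysis of the primary outcome that adds the unmatched lines identifiable in Nutritrack.

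Similar capture across arms would largely answer the concern. Different capture would show how far the primary result depends on it.

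The cost is extra coding of receipts that are already collected and partly entered by hand, with no added burden on participants. Some abbreviated receipt lines will not be matchable, so their number should be reported by arm.

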### Outcomes

The primary outcome of the trial will be the mean nutrient profiling score for all food and beverage products purchased over the four-week intervention period. Nutrient profiling score will be calculated using the Food Standards Australia New Zealand (FSANZ) nutrient profiling standard [26]. Food composition data will be obtained from Nutritrack, a brand-specific processed food composition database that contains comprehensive annually-updated information on New Zealand packaged and fast foods [27]. As a secondary approach, the crude nutrient profiling score will be transformed to a scale of 0–100 consistent across all 3 NPSC category foods. A tertiary approach will also be considered on weighted nutrient profiling score stratified by key food categories.

Secondary outcomes will be the difference between trial arms in:Mean saturated fat, total sugar, sodium and energy content per 100 g food purchases over the four-week intervention period;Mean weekly food expenditure over the four-week intervention period;Labelling profile of food purchases (mean number of HSR stars and proportions of red, green and amber traffic lights) over the four-week intervention period;Mean nutrient profiling score for all food and beverage products purchased each week of the intervention period;Mean nutrient profiling score of key food categories likely to be most impacted by nutrition labelling (e.g. breakfast cereals, cereal bars, pizzas and ready meals);Mean nutrient profiling score of the 3 nutrient profiling score criterion food categories (beverages, fats and oils, all other foods)Mean purchases of unpackaged foods (e.g. fruit and vegetables) in g/100 g;Self-reported nutrition knowledge at follow-up;Use of assigned labelling system as recorded by the Food Label Trial app.

